## Abstract

Diarrhea, soil-transmitted helminth infection and malnutrition are leading causes of child mortality in low- and middle-income countries (LMICs). To reduce the prevalence of these diseases, effective interventions for adequate water, sanitation, and hygiene (WaSH) should be implemented. This paper describes the design of a cluster-randomized controlled trial that will compare the efficacy of four school-based WaSH interventions for improving children’s health literacy, handwashing, and nutrition. Interventions consisted of (1) WaSH policy reinforcement; (2) low-, medium-, or high-volume health education; (3) hygiene supplies; and (4) WaSH facilities (e.g., toilets, urinals, handwashing basins) improvements. We randomly allocated school clusters from the intervention arm to one of four groups to compare with schools from the control arm. Primary outcomes were: children’s health literacy, physical growth, nutrition status, and handwashing prevalence. Secondary outcomes were: children’s self-reported health status and history of extreme hunger, satisfaction with WaSH facilities, and school restrooms’ WaSH adequacy. We will measure differences in pre- and post-intervention outcomes and compare these differences between control and intervention arms. This research protocol can be a blueprint for future school-based WaSH intervention studies to be conducted in LMICs. Study protocols were approved by the ethics committees of the University of Bonn, Germany, and the University of the Philippines Manila. This trial was retroactively registered, ID number: DRKS00021623.

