### 2.5. Data Collection

#### 2.5.1. Assessing Primary Intervention Outcomes

First we assessed children’s health literacy, measured by two continuous variables (hygiene literacy and handwashing literacy scores) via questionnaire (Tables S3 and S4). Second we assessed child growth, measured by continuous variables (z-scores for height-for-age [HAZ] and body mass index-for-age [BAZ]) and binary variables (prevalence of malnutrition [stunting, undernutrition, and overnutrition]), via anthropometry (Table 1). HAZ is a linear growth indicator that indicates if the child has the appropriate stature for his/her age, while BAZ is an indicator of growth that indicates if the child has the appropriate ratio of weight and height for his/her age, according to WHO guidelines [4,29,30,31,32]. We used the WHO AnthroPlus (for children 5–19 years old) software (version 3.2.2., WHO, Geneva, Switzerland) to obtain HAZ and BAZ for each child. Third we assessed handwashing prevalence via observation according to standard operating procedure (SOPs) (Figure S3).

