#### 2.5.3. Baseline Survey and Randomization

At baseline, we conducted a four-part school-based survey (Figure S3) to measure: (1) children’s health literacy and nutrition status; (2) handwashing prevalence; (3) school restrooms’ WaSH adequacy; and (4) schools’ WaSH policies. We developed a self-administered health literacy questionnaire for children in English and then translated it to Tagalog (Filipino language) (Tables S3 and S4). We made one version for primary and one version for secondary school children. The QuickTapSurvey^©^ app (Formstack LLC, Fishers, IN, USA), installed on password-protected tablets and smartphones, was used to administer all survey instruments. It is a cloud-based data collection tool that allows for simultaneous offline data entry and stamping with global positioning system (GPS) coordinates, date, and time. We applied validation rules and range limits for precise data entry.

The research supervisor conducted a full-day (8 h) initial training workshop (Table S7) for research assistants before conducting school surveys. Each school survey was conducted by a team of 5–7 rotating research assistants, directly managed by the research supervisor. To begin the school survey, we first explained the study’s aims, objectives, and methods to the children in Tagalog (Figure S3). We emphasized that participation in our study was voluntary and anonymous, and that results would remain confidential and have no impact on anyone’s school grades. Children’s full name, date of birth, and telephone number were collected and stored in a separate Microsoft© Excel spreadsheet secured in password-protected tablets. Next, we assigned children unique identification (ID) numbers and gave them each three tickets that were printed with their ID number. The ticketing system was a quality control measure that ensured that all children provided all the requested data. Children were instructed to give one ticket to the assigned research assistant at every station that they visited during the school survey (Figure S3).

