After obtaining data from the children, research assistants completed the school restroom inspection checklist, took photos of WaSH facilities, and interviewed school principals or representatives, inputting all data into the app. We obtained school administrative data, e.g., budget for maintenance and other operating expenses, from the DepEd. At the end of each workday, research assistants discussed their work with each other, shared lessons learned, and identified areas for improvement. Upon accessing an internet hotspot, we used the app to transmit anonymized data to a central database via cloud storage. Research assistants periodically checked uploaded data to verify the completeness of data upload and identify discrepant, missing, or duplicate data. When needed, appropriate remedial action was taken, e.g., re-training research assistants or clarifying instructions for children.

After completing baseline surveys, we assigned two schools to the control arm and 13 schools to the intervention arm (Figure 3). We purposefully assigned two schools to the control arm because one school had a school principal who directly asked us to participate in our previous observational study. The other school was integrated (offering all possible grade levels, from kindergarten to grade 12) and was the location where we had pilot-tested our survey instruments before the observational study. We randomly allocated schools in the intervention arm to one of four groups. One research assistant and the research supervisor conducted randomization in Microsoft^©^ Excel as follows: (1) In one column, we listed the names of the 13 schools in the intervention arm, with one row representing one school. (2) In another column, we listed the four intervention groups (A, B, C, and D), with one row representing one group. We previously determined how many schools would be allocated to each group (Table S1). (3) In a third column, we used Excel’s random number function and ranked the schools, assigning each school to either group A, B, C, or D (Table S1). Except for the research supervisor, all research assistants, study participants (children), school personnel, and parents were blinded to the assignment of schools to the intervention arm and subsequent random allocation to intervention groups A–D.

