#### 2.5.4. Follow-Up and Other Assessments

Eight months later, we conducted a follow-up assessment by implementing the same methodology (i.e., 4-part school-based survey) that we used at baseline (Figure S3) and measuring the same types of outcomes (e.g., children’s health literacy and nutrition status, handwashing prevalence, school restrooms’ WaSH adequacy, and schools’ WaSH policies). Nine months later (17 months after the first health education session), we conducted a household questionnaire for children (Table S5). Thus, we were able to assess risk factors at the individual-, school-, and home-levels (Table 2).

We expected the intervention to influence children’s knowledge, behavior, and health outcomes. We defined indicators of the intervention’s impact as changes in children’s primary and secondary outcomes. We measured the difference between outcomes from the eight-month follow-up and baseline. We compared differences between control and intervention arms. We collected samples for water quality testing from study schools and a separate sample of households (located in the school neighborhood) after post-intervention assessments, as previously reported [27].

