### 2.6. Intervention

The four parts of the intervention were: (1) WaSH policy reinforcement, (2) health education, (3) hygiene supplies, and (4) WaSH facilities improvements (Table S1). We implemented the intervention over eight months, from June 2017 to February 2018 (Figure 2). The development of the intervention was informed by findings from our previous observational study and baseline survey, as well as inputs from research assistants with expertise in the local context and stakeholders, e.g., school principals, teachers, and janitors. We also conducted opinion polls with students. It was important for us to use participatory research methods that engaged stakeholders so that we could assess whether our intervention would be acceptable or sustainable after the research project ended.

School principals were presented with a research portfolio containing recommendations for enforcing existing WaSH policies (Figure S4). We conducted one-hour hygiene promotion workshops for teachers, explaining the importance of improving WaSH in schools to achieve the United Nations’ (UN) Sustainable Development Goal (SDG) 6 [41], related to WaSH, and complying with the DepEd’s Order No. 10 [40], related to WaSH in schools. The workshop was valuable for teachers because it helped them gain new ideas about how to present to children specific health education topics, and see how big of a role classroom activities play in achieving schools’ WaSH policy goals.

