WaSH-related knowledge, attitudes, and practices (KAP) questionnaire for children	Self-reported: Demographics Perceptions about and use of school WaSH facilities Hygiene behavior (e.g., handwashing) Health history Food security	1 time: February–March 2017
Health examination (form) for children	Observed: Height Weight Urine specific gravity	3 times: February–March 2017; different sample of students during June–July 2017 and February–March 2018
Interview (form) for school principal ^(1)^	Self-reported: Perceptions about school WaSH facilities and students’ hygiene WaSH-related policies	2 times: March–June 2017; November–December 2018
School restroom inspection checklist	Observed: Availability, quantity, and quality of school WaSH facilities	2 times: February–March 2017; September–December 2018
Interview (form) for parent/guardian	Self-reported: Demographics Food security Hygiene behavior (e.g., handwashing)	1 time: March–June 2017
Home restroom inspection checklist	Observed: Availability and quality of home WaSH facilities	1 time: March–June 2017
Health literacy questionnaire for children	Self-reported: Demographics Understanding of hygiene concepts and handwashing	2 times: June–July 2017 and February–March 2018
Handwashing observation form	Observed: Children’s handwashing behavior	2 times: October 2017; February–March 2018
Water quality testing form	Observed: Indicators of water quality	1 time: April 2018 ^(2)^
Household questionnaire for children	Self-reported: Demographics Perceptions about school and home WaSH facilities Hygiene behavior (e.g., handwashing) Health and nutrition status Food security Exposure to second-hand smoke Home and household characteristics Parent/guardian’s education and employment	1 time: November 2018–February 2019
N/A	Secondary school administration data ^(3)^	Various

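### Table 2 dates the first handwashing observation to October 2017, about four months into the intervention, while the text treats it as a pre-assignment baseline for an eight-month change

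*Protocol article*

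**What the plan says.** The Abstract lists the outcome among the primary ones: "Primary outcomes were: children’s health literacy, physical growth, nutrition status, and handwashing prevalence". Section 2.5.1 says it was assessed by direct observation.

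Section 2.5.3 puts handwashing in the baseline survey: "At baseline, we conducted a four-part school-based survey (Figure S3) to measure" four things, the second of which is handwashing prevalence. The same section says that schools were assigned to arms after the baseline surveys were complete. Section 2.5.4 then defines the effect measure: "We measured the difference between outcomes from the eight-month follow-up and baseline". Section 2.8.2 repeats the idea for the mixed models, with impact estimated as the difference between pre- and post-intervention outcomes.

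Table 2 gives the dates of the handwashing observation form as "2 times: October 2017; February–March 2018". Section 2.6 states: "We implemented the intervention over eight months, from June 2017 to February 2018 (Figure 2". Section 2.5.4 places the household questionnaire "17 months after the first health education session", and the note to Figure 2 dates that questionnaire to November 2018.

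On blinding, Section 2.5.3 says: "Except for the research supervisor, all research assistants, study participants (children), school personnel, and parents were blinded to the assignment of schools". A few lines earlier it says that one research assistant, with the research supervisor, carried out the randomisation.

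**The concern.** The narrative and the data collection table cannot both be right for this outcome. If Table 2 is correct, the value to be used as the pre-intervention measurement was taken while the intervention was under way. Handwashing was taught directly in the education sessions (Section 2.6), so it is an outcome that could move early. A change score or a pre-post mixed model would remove whatever between-arm difference had arisen by October, and using the October value as a covariate would condition on something measured after allocation. A null handwashing result could then be read as absence of effect when part of the effect had been differenced away. The limitations in Section 3 do not mention this.

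**Working it through.** **Check the start date.** Three stated intervals can be tested by counting calendar months.
- June 2017 to February 2018 = 8 months, as Section 2.6 says.
- February 2018 to November 2018 = 9 months, as Section 2.5.4 says for the household questionnaire.
- June 2017 to November 2018 = 17 months, as Section 2.5.4 and the note to Figure 2 say.

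All three agree, so June 2017 is a consistent start for both the intervention and the first education session.

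**Place the handwashing observations on that timeline.**
- June 2017 to October 2017 = 4 months (3 if counted from July). The first observation is about halfway through the eight months.
- October 2017 to February–March 2018 = 4 to 5 months, against the eight months stated for follow-up minus baseline.

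**Compare with the other child-level instruments in Table 2.** The health literacy questionnaire and the health examination of the trial sample are dated June–July 2017 and February–March 2018, an interval of 8 months. They fit the narrative; the handwashing row does not. Earlier handwashing data exist only as self-report, in the February–March 2017 KAP questionnaire and the March–June 2017 parent interview. The KAP questionnaire belongs to the observational study, whose students were not re-recruited (Section 2.3). Neither supplies an observed baseline.

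**What the change contrast would estimate.** Let δ be the between-arm difference in handwashing before any intervention, D_O the difference caused by October 2017, and D_F the difference caused by February–March 2018.
- Planned contrast with a true baseline: (δ + D_F) − δ = D_F.
- Contrast with October as baseline: (δ + D_F) − (δ + D_O) = D_F − D_O.
- Bias = −D_O.
- Contrast using only the final observation: δ + D_F.

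If the intervention had raised handwashing relative to control by October, D_O is positive and the bias is downward. The article gives no value for D_O. The last line shows the price of dropping the first observation: the contrast is unbiased only where δ is zero in expectation. Randomisation provides that among groups A–D but not against the two control schools, which were assigned purposively.

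**The case against.** The strongest reply is that Table 2 may be the faulty source. It does not call October a baseline, and the text says handwashing was measured before assignment. Other rows also depart from the narrative: restroom inspections are dated February–March 2017 and September–December 2018, and principal interviews March–June 2017 and November–December 2018. These rows cut both ways. They may mean the table is unreliable, or that the parts of the survey really were done at different times. The objection stands to this extent: the article shows a conflict, not proof that the baseline was taken in October.

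A reader might also infer more than the article supports, in four respects.
- **A quantified loss.** One could say that roughly half the effect is lost under linear build-up, or all of it if the first sessions produced it. But control schools also received policy reinforcement, a teacher workshop and two education sessions (Section 2.1). Only the differential content matters, and the text shown does not say how much of it had been delivered by October. No percentage follows. A reversal of sign would need early gains that later faded, and nothing in the article points to that.
- **Contaminated literacy and growth baselines.** A June first session falls within the June–July survey window, but these are month-level dates across schools. Nothing shows that any child was surveyed after a session.
- **All research assistants unblinded.** The contradiction is shown only for the one who took part in randomisation. The article does not say who observed handwashing, survey teams rotated, and delivering a session does not by itself reveal the arm, since controls had sessions too.
- **A covariate-adjusted final comparison as the remedy.** With 15 schools, five groups and two purposively chosen controls, replacing the change analysis by a model with several school-level covariates is a debatable trade, not a clear correction.

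**Conclusion.** The point holds in this form: the article describes observed handwashing as a pre-assignment baseline with an eight-month pre-post change, while its own dates put the first observation about four months after the start and 4 to 5 months before the last. Taken at face value, those dates leave a primary outcome with no observed pre-intervention value, and the planned change would not estimate the effect of the whole intervention. The bias is of unknown size and probably toward zero, on the assumption that some differential effect had arisen by October. The conclusion rests on the Table 2 date being right; if it is an error, the correction is to the table alone. Either way, the conflict should be settled before handwashing is analysed. The blinding statement is wrong for one research assistant, and no wider claim is established.

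**What to change.** 1. Check the October 2017 date against the date and time stamps that the survey app records (Section 2.5.3), and reconcile Table 2 with Sections 2.5.3 and 2.5.4.
2. If October 2017 is confirmed:
   - label it a mid-intervention observation;
   - do not use it as the pre-intervention value, or as a baseline covariate, in the change or mixed-model analysis;
   - report February–March 2018 prevalence by group, relying mainly on comparisons among the randomised groups A–D;
   - report the comparison with the two control schools as unadjusted for baseline handwashing and open to confounding;
   - present the October to February–March difference only as a mid-to-end change.
3. If the date is wrong, correct Table 2; the planned handwashing change can then stand as regards timing.
4. Correct the blinding statement in Section 2.5.3 so that it excepts the research assistant who took part in the randomisation.

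The cost is a check of stored records plus changes to wording and analysis; no new data are needed. If October stands, there is also a loss of information. Comparisons among A–D rest on 13 schools in four groups, and the contrast with control loses its protection against pre-existing differences. That limitation should be stated with the results.

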
## Data Availability

Not applicable.
